### Statistical considerations

All variables will be descriptively analyzed with the appropriate statistical methods: for categorical variables using frequency tables and for continuous variables with sample statistics (e.g., mean, median, standard deviation, minimum and maximum value, 25° and 75° quartile).

Unless otherwise specified, all statistical tests will be 2-tailed and at a 5% significance level.

All the primary and secondary efficacy and safety analyses will be performed in the modified intention-to-treat (ITT) population, including all randomized subjects who received at least one dose of the study drug.

Further supporting analysis will be performed in the per-protocol population, which will include all randomized subjects who were complying with treatment, that is, taking at least 65% of the intended dose units of the study drug.

Subjects who are randomized and who have taken any amount of study drug will not be replaced for any reason. Subjects who will be randomized but withdraw their consent before taking the study drug may be replaced, although they will not lose their unique identifier.

Subjects who leave the observation without manifesting the endpoint will be considered censored, participating in the risk during the observation period. For subjects who do not appear for clinical evaluations at 12 and 24 months of observation, every effort will be made to know a possible outcome of interest for the study, making them evaluable for endpoints.

### Treatment compliance

Compliance with oral treatment can be used as a stratification variable (< 65% and >  = 65%) and defined as compliance = the total number of tablets actually taken / the total number of tablets expected*100.

### Final analysis of the primary endpoints

The primary cumulative efficacy endpoint will be the occurrence of the first event among the event types considered. The hypothesis of superiority of the primary cumulative efficacy endpoint will be tested by multivariate Cox proportional hazards regression using as covariates the assigned drug, age at randomization, sex, compliance with treatment, and the additional risk factors for DVT and DVT/PE found to be significantly associated in the univariate analysis (between obesity, varicose veins, cancer, standing or prolonged immobilization, recent surgery, severe infections, prior DVT/PE, thrombophilia, chronic heart failure NYHA III-IV, use of estrogen-progestogens). All variables participating in the model will be tested for the assumption of proportionality of the risks with the usual graphical method. In addition, a significant subset of variables will be chosen with the Wald method and in a “forward stepwise.”

The crude and adjusted cumulative proportion of event-free subjects over follow-up in the two treatment groups will be described with Kaplan–Meier plots.

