### Statistical analysis and sample size

From the available data in the literature we hypothesize a risk of the occurrence of the primary efficacy outcome in the placebo group at the end of the treatment of 15% (that is, a cumulative proportion of 85% of subjects without events) and a 50% decrease in risk in the mesoglycan group (HR = 0.5) [3, 5, 9].

A two-sided log-rank test with an overall sample size of 650 subjects (of which 325 are in the placebo reference group and 325 in the mesoglycan treatment group) achieves a power of 90%, at a significance level (alpha) of 0.025, to identify a difference of 7.2%, between 15.0 and 7.8% (the proportions of subjects with primary endpoint in the placebo and mesoglycan group, respectively) after 12 months of treatment. This corresponds to a hazard ratio (HR) = 0.50. Subjects will be enrolled in the study for 24 months, and 50% of enrollments will be completed in month 12. The calculation considers the loss of subjects enrolled during follow-up of 10.0% in the placebo group and 10.0% in the mesoglycan group. 650 subjects will be enrolled and randomized 1:1 in the two placebo and mesoglycan arms.

This number seems large enough to guarantee the study an adequate “power” (> 0.80) even if the risk of observing the primary endpoint in the placebo group (hazard rate control) is the difference in efficacy between the two treatments (hazard ratio) that will deviate significantly from those hypothesized.

However, an “interim-analysis” is prepared when 3/4 of the subjects (n = 488) are enrolled so that the “Data and Safety Monitoring Committee” can reformulate the number of subjects to be enrolled (“resampling”) to reach the preset study power (90%) if the number of primary endpoint events observed up to then deviates significantly from the expected for the two groups, i.e., if the HR differs from the estimated one (50%) exceeded 5% in absolute value (a lower deviation seems tolerable based on the above simulation).

The alpha error is, therefore, conservatively set at 0.025 (O'Brien-Fleming method).

For the interim analysis, a tabular description of the frequency of the primary efficacy endpoint will be provided to the Committee, stratified by treatment group but without its label (i.e., without identifying the nature of the treatment assigned to each group).

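### The primary Cox model adjusts for treatment compliance, which is measured after randomisation, and leaves its baseline covariates to be chosen from the trial data

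*Protocol article*

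**What the plan says.** Under Final analysis of the primary endpoints, superiority is tested by a multivariable Cox regression "using as covariates the assigned drug, age at randomization, sex, compliance with treatment, and the additional risk factors for DVT and DVT/PE". The risk factors come from a printed list of ten and enter if "found to be significantly associated in the univariate analysis". The section then adds that "a significant subset of variables will be chosen with the Wald method", in a forward stepwise procedure. It does not say that the treatment term is kept during that step.

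Treatment compliance defines the ratio as "the total number of tablets actually taken / the total number of tablets expected*100", with a cut at 65%, but gives no period over which tablets are expected. Patient flow has compliance assessed at the visits at months 3, 6, 9 and 12.

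Statistical considerations places all efficacy analyses in a modified ITT population (randomised, at least one dose). It adds a supporting per-protocol set of subjects "taking at least 65% of the intended dose units of the study drug".

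No unadjusted test is named for the final primary analysis. The Kaplan–Meier plots there are descriptive, and the log-rank test under Final analysis of secondary endpoints is for those endpoints. The only other log-rank test is in the sample-size calculation: "A two-sided log-rank test with an overall sample size of 650 subjects".

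**The concern.** Randomisation makes the arms comparable on what precedes it. Compliance comes afterwards. If mesoglycan is tolerated differently from placebo, or if patients with a worse prognosis take fewer capsules, compliers in one arm are not comparable with compliers in the other. A model that conditions on compliance then mixes the drug effect with that selection. The modified ITT population does not prevent this, because the selection is brought back through the covariate.

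A second route is possible. If expected tablets cover the full 12 months and study drug stops at an event, an early event itself produces low compliance, and the model adjusts for a consequence of the outcome.

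What is at stake is the test that decides the trial: its hazard ratio, its type I error and its power. The data-driven choice of baseline covariates is a lesser matter. It leaves open which model is the confirmatory one until outcomes have been seen.

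**Working it through.** **Inputs.** From Statistical analysis and sample size: 325 patients per arm, 12-month risk 15.0% on placebo and 7.8% on mesoglycan, HR 0.50, two-sided alpha 0.025, 10% loss per arm. From Treatment compliance: the 65% cut. From Treatment: 12 months of dosing. Assumed here: exponential event times and 10% loss as an annual rate.

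**The plan's own figures.** 1 − 0.85^0.5 = 7.8%, so the two risks agree with HR 0.50. With hazards 0.1625 (−ln 0.85) and 0.0813 and loss hazard 0.1054 (−ln 0.90), expected 12-month events are:
- placebo: 325 × 0.1625/0.2679 × (1 − e^−0.2679) = 46.3
- mesoglycan: 325 × 0.0813/0.1866 × (1 − e^−0.1866) = 24.1
- total: 70.4

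Schoenfeld power is Φ(√70.4/2 × ln 2 − 2.2414) = Φ(0.667) = 75%. The stated 90% would need 4(2.2414 + 1.2816)²/(ln 2)² = 103.3, so 104 events. That gap is a separate matter. It is shown only because it explains why the reference power below is about 70% and not 90%.

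**When could a fully adherent patient reach 65%?** If expected tablets mean a 12-month supply and drug stops at the event, at 0.65 × 12 = 7.8 months. Share of 12-month events before then:
- placebo: (1 − 0.85^0.65)/0.15 = 0.1002/0.15 = 66.8%
- mesoglycan: (1 − 0.85^0.325)/0.0780 = 0.0514/0.0780 = 65.9%

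On that reading about two thirds of patients with an event are classed as non-compliant, and they also leave the per-protocol set.

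**Effect on the treatment term.** Simulated trials of 650 patients followed for 12 months, with 1,000 to 4,000 runs per scenario. Monte Carlo error is about 0.2–0.4 points on type I error and 1–1.5 points on power. Each cell gives the Cox model with treatment alone → the model with compliance (≥65%) added.

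| Assumption about compliance | HR, true 0.50 | Power | Type I error |
|---|---|---|---|
| Unrelated to arm and outcome, 15% non-compliant | 0.49 → 0.49 | 72% → 71% | 2.6% → 2.6% |
| Expected tablets counted only to the event, almost all compliant | 0.49 → 0.50 | 71% → 71% | 1.9% → 2.0% |
| 12-month supply, half of events stop drug, 15% background | 0.49 → 0.50 | 72% → 69% | 2.6% → 2.5% |
| 12-month supply, every event stops drug, 15% background | 0.50 → 0.53 | 70% → 60% | 2.4% → 3.1% |
| 12-month supply, every event stops drug, background near zero | 0.50 → 0.71 | 71% → 24% | 2.2% → 7.2% |
| Linked to prognosis only, compliers 84% in both arms | 0.51 → 0.51 | 66% → 67% | 2.3% → 2.6% |
| Linked to prognosis, compliers 84% placebo, 76% mesoglycan | 0.50 → 0.47 | 69% → 75% | 2.3% → 2.5% |
| Linked to prognosis, compliers 84% placebo, 66% mesoglycan | 0.50 → 0.44 | 69% → 82% | 2.5% → 4.4% |

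In the last two rows a true HR of 1.00 is estimated at 0.95 and 0.89. The bias can therefore favour mesoglycan as well as hide its effect. In those two rows the drug does not stop at the event, so the bias there does not need the outcome to affect compliance.

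**Effect of choosing baseline covariates.** Univariate selection among ten baseline factors, with treatment retained, compared with treatment alone: type I error 2.5% against 2.2%, HR 0.51 against 0.51, power 70% against 71%. Forward stepwise Wald selection with treatment retained gave type I error 2.2%, HR 0.50, and power 71% against 68% unadjusted.

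**The case against.** A reader might infer four stronger criticisms that the article does not support.

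- **Compliance is driven by the outcome, so the drug effect is absorbed.** This needs both a 12-month denominator and drug stopping at the event, and the article fixes neither. The Abstract suggests that an event ends follow-up, since only patients without a primary outcome are followed on, but that does not settle how tablets are counted. With counting to the event the simulated bias vanished. Any figure for events lost from the per-protocol set rests on the same condition, and that set is only supporting.
- **The bias lowers power.** The table shows either direction, or none. Larger losses could be obtained by entering compliance as a continuous percentage, but the only form the article gives is the split at 65%.
- **Stepwise selection makes the treatment p-value invalid.** The simulations do not show this for the treatment term when it is retained. The ten candidates are listed in advance, and the stepwise sentence can be read as a further model, in which case treatment stays in the main one.
- **Sizing on a log-rank test and analysing with an adjusted Cox model is an error.** It is common practice. Adjusting for age and sex is also sound, because they are the stratification factors.

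These objections leave the core untouched. Compliance is named as a covariate in the deciding test, it is observed after randomisation, and no other primary test is given. This is a stated rule, not a detail left to an unseen analysis plan.

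**Conclusion.** The point holds in this form. Compliance does not belong in the primary model, because it can bias the treatment hazard ratio in either direction. Across the assumptions tried, a true HR of 0.50 was estimated between 0.44 and 0.71, and type I error rose from about 2.5% to 4.4% or 7.2% at worst. These are illustrations under stated assumptions, not predictions for this trial. Little or no bias arises if compliance is unrelated to arm and prognosis and expected tablets are counted only to the event, but the article guarantees neither. Early events count as non-compliance, and leave the per-protocol set, only under the 12-month denominator with drug stopped at the event. The selection of baseline covariates is secondary: it has little numerical effect if treatment is retained, but it leaves the confirmatory model undefined until the outcomes are known.

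**What to change.** - Remove compliance from the primary model.
- Make the primary test the treatment effect from a Cox model with assigned treatment, age and sex, plus any baseline factors fixed in advance. A log-rank test stratified by the randomisation factors would serve equally well.
- State that treatment is always in the model.
- Move the compliance-adjusted and stepwise models to exploratory analyses.
- For the compliance ratio and the per-protocol set, count expected units only to the earliest of event, censoring or month 12.

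The cost is a change of analysis wording before unblinding. No new data, visits or patients are needed. The Abstract places the final analysis at the end of 2024. If unblinding has already taken place, the change should be reported as made afterwards, with both analyses shown.

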### Final analysis of secondary endpoints

For the analysis of the secondary efficacy endpoints, the following will be used:the Kaplan–Meier plot of the cumulative occurrence over time and the log-rank test to compare the two treatment arms,for the rVCSS scores, analysis of variance for repeated measures will be used (all available assessments for within-subject effects and the 2 treatment groups as between-subjects effect).in the case of the VEINES/Sym-Qol scores, the analysis of variance for repeated measures will be used (all evaluations available for the within-subject effect and the 2 treatment groups as the between-subjects effect).The impact of elastic compression therapy in the various endpoints will be analyzed by inserting it as a stratification factor in the related analyzes.The predictive contribution of CRP levels (subdivided by tertiles) to the primary efficacy endpoint will be analyzed by insertion as a stratification factor in relative analyzes.

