The included patient will first undergo bilateral color-coded Doppler ultrasound (CCDU) of the lower limbs to exclude concomitant involvement of the deep venous system or an extension of the index SVT. Furthermore, blood sampling for alanine-aminotransferase, aspartate-aminotransferase, creatinine, complete blood count, prothrombin time, activated partial thromboplastin time, and C-reactive protein will be performed.

A computer-based centralized randomization, with 1:1 allocation between mesoglycan and placebo, and random variable size blocks (4 to 6 units), stratified for age (< 60 y, >  = 60 y), and gender (F/M), will be run through a dedicated application (REDCAp). Patient recruitment is expected to be completed in 24 months.

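### The secondary analyses do not use the age and sex strata of the randomisation: a minor, avoidable loss of precision, mainly for the rVCSS and VEINES/Sym-QoL scores

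*Protocol article*

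**What the plan says.** The section Study population and randomization of the protocol article sets 1:1 central allocation with "random variable size blocks (4 to 6 units), stratified for age" (cut at 60 years) and by gender. That makes four strata.

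The section Final analysis of secondary endpoints then gives these analyses:

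- Event outcomes: a Kaplan–Meier plot and "the log-rank test to compare the two treatment arms".
- rVCSS: repeated-measures analysis of variance, with "all available assessments for within-subject effects and the 2 treatment groups as between-subjects effect".
- VEINES/Sym-QoL: the same method, with "all evaluations available for the within-subject effect and the 2 treatment groups as the between-subjects effect".
- Stratification factors: the section names two, each for its own question. One is compression ("The impact of elastic compression therapy in the various endpoints will be analyzed by inserting it as a stratification factor"); the other is CRP in tertiles.

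The randomisation factors appear in none of these. By contrast, the Cox model in Final analysis of the primary endpoints lists age at randomisation and sex among its covariates. Statistical considerations sets a two-tailed 5% level unless otherwise specified.

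**The concern.** Stratified allocation balances the arms within each age-by-sex stratum, so differences between strata contribute almost nothing to the chance variation of the treatment difference. A model with treatment alone does not know this. It leaves the between-stratum variation in its error term and reports a standard error larger than the true one. The test is then conservative and power is lost.

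The same two variables are in the primary model and absent from the secondary models, with no reason given. The Introduction names male sex as a risk factor for thromboembolic complications and reports that SVT incidence varies with age and sex, so it is plausible that the strata matter for at least some outcomes. The Abstract reports 570 patients randomised against 650 planned, so precision is already below plan.

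**Working it through.** The documents state no power or precision figure for the secondary analyses, so there is none to reproduce. The check concerns the size of the loss.

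**Inputs.** From the documents: 1:1 allocation, four strata, blocks of 4 to 6, N = 650 planned and 570 randomised, two-sided 5% level. Not in the documents: the share of score variance explained by age group and sex, called R². Assumed range: 0 to 0.20.

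**1. Scores, between-subjects treatment comparison.** Let σ² be the total variance of a patient's score.

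- Standard error from the treatment-only model: √(4σ²/N).
- Actual standard error under balance within strata: √(4σ²(1 − R²)/N).
- Ratio: 1/√(1 − R²).
- Actual level of the nominal 5% test: 2Φ(−1.96/√(1 − R²)).

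With N = 650 and σ = 1, the treatment-only standard error is √(4/650) = 0.0784.

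| R² | Ratio of standard errors | 1.96 × ratio | Actual level |
|---|---|---|---|
| 0 | 1.000 | 1.960 | 5.0% |
| 0.05 | 1.026 | 2.011 | 4.4% |
| 0.10 | 1.054 | 2.066 | 3.9% |
| 0.20 | 1.118 | 2.191 | 2.8% |

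A simulation of 650 patients (permuted blocks of 4 or 6 within the four strata, one time point standing in for the between-subjects test, 1,500 runs per setting) agrees. At R² = 0.10 the treatment-only model reports 0.0784, while the estimate actually varies with standard deviation 0.0742; the model with strata reports 0.0744. At R² = 0.20 the three figures are 0.0784, 0.0714 and 0.0701. Power at an illustrative effect of 0.22 SD, treatment-only against adjusted, is 0.82 against 0.84 (R² = 0.05), 0.82 against 0.85 (0.10) and 0.84 against 0.89 (0.20). At R² = 0 it is 0.80 for both.

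**2. Scores, treatment-by-time test.** A stratum effect that is the same at every visit is part of the patient's overall level and cancels from within-patient changes. In a simulation with N = 570, two visits, constant stratum effects and 20,000 runs, the level of this test was 4.9%, 4.9% and 4.8% at R² = 0.05, 0.10 and 0.20. The level of the between-subjects test in that design was 4.3%, 3.9% and 3.0%, in line with the table.

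**3. Secondary log-rank tests.** The simulation used N = 650, 12 months, 10% loss and a two-sided 5% level, with 2,000 runs per setting. The share of women was 58.8% (Abstract); the share aged 60 or over was assumed to be 64.1%. Placebo risks and treatment hazard ratios are illustrative, because the documents give none for these outcomes.

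| Hazard ratio, age group / sex | Placebo risk, treatment HR | Power unstratified | Power stratified | Gain (points) |
|---|---|---|---|---|
| 1 / 1 | 15%, 0.5 | 0.8055 | 0.8050 | −0.05 |
| 1 / 1 | 30%, 0.6 | 0.8870 | 0.8850 | −0.2 |
| 1.5 / 1.5 | 15%, 0.5 | 0.8125 | 0.8170 | 0.45 |
| 1.5 / 1.5 | 30%, 0.6 | 0.8760 | 0.8840 | 0.8 |
| 2 / 2 | 15%, 0.5 | 0.8155 | 0.8210 | 0.55 |
| 2 / 2 | 30%, 0.6 | 0.8580 | 0.8705 | 1.25 |
| 3 / 2 | 15%, 0.5 | 0.8010 | 0.8065 | 0.55 |
| 3 / 2 | 30%, 0.6 | 0.8635 | 0.8785 | 1.5 |

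With no treatment effect and strongly prognostic strata (3 / 2), the unstratified test rejects in about 4.1% of trials and the stratified test in 4.9% to 5.2%.

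**The case against.** The strongest reply is that nothing in the section is wrong. A comparison by arm alone is valid, and any error is on the cautious side. The article condenses a fuller protocol, and covariates for secondary analyses are often settled in the analysis plan. The text never calls the log-rank test unstratified and never says that treatment is the sole between-subjects effect. The evidence on male sex concerns thromboembolic events, where stratifying gains little; nothing in the documents says that age group or sex predicts either score. The plan also does not say whether the main effect or the treatment-by-time term is the test of interest, and the latter is hardly touched.

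Most of this stands and limits the size of the point. It does not remove it. The section goes beyond silence: it spells out the effects in both score models and names stratification factors where the authors want them, and the randomisation factors are not among them. The primary model already carries age and sex, so including them in the secondary analyses would follow the article's own practice.

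**Conclusion.** The point holds as a minor matter of efficiency on secondary outcomes. For the between-subjects comparison of the two scores, the standard error is too large by 0% to about 12% and the nominal 5% test runs at 5.0% to about 2.8%, for an assumed R² of 0 to 0.20. If age group and sex do not predict the scores, nothing is lost. The treatment-by-time test is largely unaffected if stratum effects are constant over time. For the log-rank tests the gain is at most about 1.5 power points in the settings tried.

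Three stronger readings are tempting, and the documents do not support them:

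- A reader might infer that all the secondary tests run below 5%. That holds only where the strata are prognostic for the outcome and the test is a between-patient one.
- A reader might infer bias or false-positive findings. The omission causes neither.
- A reader might turn the loss into patients: 570 × (1/(1 − R²) − 1) gives 30 at R² = 0.05 and 63 at 0.10. Those are equivalents in interval width at an assumed R². The section specifies no intervals, and the equivalents in power are smaller.

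**What to change.** In Final analysis of secondary endpoints, add age stratum and sex as between-subject factors in the rVCSS and VEINES/Sym-QoL models, and state whether the treatment main effect or the treatment-by-time term is the test. For consistency with the design and the primary model, stratify the secondary log-rank tests by the four randomisation strata.

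The cost is a few words in the plan and a line of code. Both variables are already in the randomisation system, and with four strata no material downside is expected: with no stratum effect at all, the stratified and plain log-rank tests had practically the same power. The change should be fixed before the blind is opened after database lock.

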### Patient flow

Medical control visits will be scheduled 3, 6, 9, and 12 months after randomization for every included patient, during which a complete evaluation of their clinical status, compliance with treatment, concomitant treatments and adverse events will be performed. At each visit, patients will also receive the revised Venous Clinical Severity Score (rVCSS), which accounts for changes in disease severity over time and in response to treatment, and the VEINES/Sym-QoL questionnaire, a disease-specific quality of life instrument for chronic venous disorders of the leg [34–39]. A CCDU examination and a blood sample will also be scheduled for the 12 month visit.

At the end of the 12-month treatment cycle, patients will enter another 12-month clinical follow-up period, during which they should not receive any experimental treatment; for a total study time of 24 months. A final visit will be scheduled 24 months after randomization in patients who complete the study course.

Patients who meet exclusion criteria at any time during the study, become pregnant, do not comply with study purposes or withdraw their consent will be censored. Patients who withdraw experimental treatment will continue to observe according to the study protocol until the end of the study. The planned flow of the patient is shown in Fig. 1.

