### Study outcomes

The *primary efficacy outcome* of the study will be an objectively documented symptomatic recurrence or extension of SVT, symptomatic DVT (proximal or distal), asymptomatic proximal DVT, symptomatic pulmonary embolism (fatal / nonfatal), or death, whichever comes first, during the treatment period.

The *secondary efficacy outcome* will be: the occurrence of asymptomatic recurrence, extension, or asymptomatic distal DVT; the rVCSS score and the VEINES / Sym-QoL questionnaire; the impact of elastic compression therapy on SVT treatment; the association between CRP levels and primary efficacy outcomes; the natural history of SVT in patients allocated to placebo; the evaluation of the prolonged protective effect of mesoglycan after the first 12 months of treatment.

The *safety outcome* will be the incidence of major bleeding, as defined by the International Society on Thrombosis and Hemostasis (ISTH) criteria: fatal and/or symptomatic bleeding in a critical area or organ (e.g., intracranial, intraspinal, intraocular, retroperitoneal, intraarticular, pericardial, intramuscular with the associated compartmental syndrome); and/or in the case of clinically overt bleeding associated with a hemoglobin decrease of at least 20 g/L or requiring transfusion of 2 or more units of packed red blood cells [40].

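### Entering elastic compression only as a stratification factor does not estimate its impact, which is a listed secondary outcome, and comparing the strata instead would be confounded

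*Protocol article*

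**What the plan says.** Under Study outcomes, the protocol article lists "the impact of elastic compression therapy on SVT treatment" among the secondary efficacy outcomes. Under Final analysis of secondary endpoints, one sentence gives the method: "The impact of elastic compression therapy in the various endpoints will be analyzed by inserting it as a stratification factor in the related analyzes". The analyses to which this factor would be added are, in the same section, Kaplan–Meier plots with "the log-rank test to compare the two treatment arms", and repeated-measures analysis of variance for the rVCSS and VEINES/Sym-QoL scores.

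Under Study population and randomization, patients are randomised "with 1:1 allocation between mesoglycan and placebo", in "random variable size blocks (4 to 6 units), stratified for age" and by gender. Compression is neither allocated nor a randomisation stratum.

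On data collection, the Patient flow section says: "Medical control visits will be scheduled 3, 6, 9, and 12 months after randomization for every included patient". At these visits an evaluation of "compliance with treatment, concomitant treatments and adverse events will be performed". Compression is not named there. Nowhere does the article say whether the compression stratum means use at baseline, current use or ever-use.

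**The concern.** An impact is an effect to be estimated. A stratification factor is a device for removing a variable's influence from another comparison. The plan names the first as an outcome and supplies only the second as its analysis.

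Two things could follow. Applied literally, the event-type analyses would leave a declared secondary outcome without an estimate. Alternatively, someone would compare patients with and without compression across the strata and read the difference as the impact. Patients who wear stockings are likely to differ from those who do not in varicose disease, earlier thrombosis and symptoms, so that difference is not the effect of the stockings. If use begun after randomisation also counts, the order of exposure and outcome is no longer fixed, and the result could be an artefact mistaken for evidence about compression.

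**Working it through.** The plan states no figure on this point, so there is none to reproduce. The check has three steps.

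**1. What the stated method returns.** A stratified log-rank statistic sums, over compression strata, the observed minus expected events in one arm. A stratified Cox model gives each stratum its own unspecified baseline hazard. Neither contains a compression parameter. A stratified Cox model with treatment as covariate, fitted to simulated data, returned one coefficient, for mesoglycan. In the repeated-measures analysis of variance, a compression term would appear if compression were entered as a further between-subjects factor, but it would then be the unadjusted, non-randomised comparison of step 2.

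**2. What a comparison of strata returns, by arithmetic.** Suppose compression has no effect and use at any time counts.

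- From the sample-size section: risks of 15.0% and 7.8%, so pooled p = (15.0 + 7.8)/2 = 11.4%.
- Assumed, not in the documents: share b using compression from the start, and share s of non-users with an event who start afterwards.
- Share classed as users: U = b + (1−b)·p·s.
- Risk in users: [p·b + (1−b)·p·s]/U.
- Risk in non-users: (1−b)·p·(1−s)/(1−U).

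With b = 0.30 and s = 0.25, U = 0.30 + 0.70 × 0.114 × 0.25 = 0.320. The risks are 0.0542/0.320 = 16.9% and 0.0599/0.680 = 8.8%, a risk ratio of 1.92. With s = 0.50 the risks are 21.8% and 6.0%, a risk ratio of 3.61. For b from 0.20 to 0.50 and s from 0.25 to 0.50, the ratio runs from 1.57 to 4.61. This formula allows only starts after an event.

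**3. Starts before an event as well, by simulation.** Inputs from the sample-size section: 12-month placebo risk 15% and mesoglycan hazard ratio 0.50, with exponential event times. The true compression effect is zero. Assumed: 30% or 50% use at baseline; 0, 20% or 40% of the rest starting before any event; 0, 30% or 60% of remaining non-users with an event starting afterwards.

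| Classification and pattern | Apparent rate ratio, users to non-users |
|---|---|
| Ever-use, no later starts | 0.99 to 1.01 |
| Ever-use, starts only after an event | 1.80 to 5.30 |
| Ever-use, starts only before any event | 0.60 to 0.82 |
| Ever-use, both kinds of start | 1.08 to 3.56 |
| Use at baseline, all patterns | 0.98 to 1.02 |

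The second row is reverse causation: the event leads to the exposure. The third is immortal time: a patient must stay event-free long enough to start. Baseline classification removes both. It does not remove confounding by indication, which was not simulated.

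In the same scenarios, stratifying by ever-use moved the mesoglycan hazard ratio by at most about 0.02 (for example 0.48 against 0.46). No effect of the drug on uptake of stockings was simulated.

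**The case against.** The strongest reply is that the article does not commit to a faulty definition. It mentions concomitant treatments without naming compression, and it describes a screening visit without listing everything recorded there. Classification at baseline is therefore not excluded, and the exposure window of a secondary covariate is commonly left to the SAP. This stands, and the timing bias is accordingly conditional.

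A reader might infer that stockings would come out as harmful. The documents do not support that. The stratified test returns no compression estimate, so by itself it shows neither harm nor benefit. If strata are compared, the direction depends on when stockings are started. Starts after a primary event may also be recorded only in part: the Abstract can be read as ending follow-up at a primary outcome, and the primary outcome includes death, after which nobody starts stockings. The formula in step 2 ignores both.

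A reader might also infer that the comparisons between arms would be spoiled. Conditioning on a variable that treatment could influence is unsound in principle, but no material distortion appeared in the scenarios run.

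Finally, the outcome could mean whether results differ by compression use, for which stratified presentation is an ordinary description. That is a fair reading, but it too needs a defined classification and a treatment-by-compression term, and the text gives neither.

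None of this answers the main point. The method is stated, and for the event-type endpoints it does not produce the quantity named as the outcome.

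**Conclusion.** The concern holds in this form: the stated analysis does not estimate the impact of compression, and the obvious substitute, comparing the strata, is confounded because compression is not randomised. The mismatch between outcome and method rests on the text alone and needs no assumption about usage.

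The further bias from timing applies only if use after randomisation counts, which the article does not say. Its direction is open and its size depends on usage that the documents do not give. The ratios above illustrate what could happen and do not predict this trial's result.

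The point concerns one secondary outcome. The primary Cox model does not list compression among its covariates, and the primary conclusion is not affected.

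**What to change.** Replace the sentence on compression with a defined exposure and a model that estimates its association with outcome:

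- Classify compression by use at randomisation. If later use is of interest, use a time-updated covariate that counts only use before the event.
- Enter it as a main effect, with a treatment-by-compression interaction, in the Cox model for event endpoints and in the repeated-measures model for the scores.
- Adjust for baseline risk factors that the plan already lists for the primary model, such as varicose veins and prior DVT/PE.
- Report the result as an observational association.
- Keep compression begun after randomisation out of the strata used to compare the arms.

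The cost is a few lines of text and one extra model. In the baseline version, patients who start later count as non-users, which may dilute an association. Confounding by indication is reduced by adjustment but not removed.
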